## Methods

### Sample size, inclusion & exclusion criteria

Sample Size is determined by two means; literature has worked with sample sizes averages between 10–40 participants, due to the long training period and evaluation requirements [30,31]. Sample size was calculated determining F-tests family for ANOVA repeated measures between and within interactions, given a moderate effect size of 0.25, alpha error prob of 0.05 and power of 0.80, two groups and two measurements. Effect size was determined with related previous works, where effect sizes of behavioral auditory discrimination measurements are reported from moderate to large, based on Cohen’s d and Cohen’s f calculations [32–35]. Larger effects sizes have been suggested when individuals were submitted for first time to auditory devices [36].

G*Power 3.1 points a total sample size for both groups of 34. Considering two independent groups for auditory discrimination training (ADT) implementation, sample size for Group A (control), and Group B (experimental) will be equally distributed.

A total of 40 participants will be recruited and enrolled in the study, as described in Fig 1, predicting a sample rejection of ~10%. Each of them will be randomly assigned to one of two groups (control group or experimental group) depending on the training methodology they will receive. Sample size for each group (non-game-based ADT and game-based ADT) is 20 individuals each. Assignments of each participant will be randomized using simple randomization 1:1 allocation ratio to select the group for the training methodology, avoiding bias on trials.

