### Expected outcomes & analysis

The primary outcome measures are related to neuro audiological changes in auditory processing. AEPs to be obtained are Mismatch Negativity and P3 components (continuous). Additionally, number of discrimination trials (discrete) will be registered. The secondary outcome measures are the in-game indicators such as time in each activity (continuous), accuracy (discrete) and attempts (discrete) to relate directly changes in audiological measures and game performance. The expected outcome of ADPQ is to increase the average score, that indicates a better perceived state and performance in auditory discrimination tasks that would be correlated with the in-game indicators and the electrophysiological measurements. The expected comparison outcome for AEP, it is expected an increase in evoked potentials amplitude and a decrease in latencies. For the in-game indicators it is expected to increase accuracy answers and decrease tasks’ solving time.

Once obtained and processed KPIs and discrimination threshold results, data will be analyzed with the following tools. Each of them will compare before and after auditory training KPIs and AEPs tests.

A 2-way analysis of variance (ANOVA) with repeated measures will be done considering the following factors.

For pre & post training measurements to determine individual performance of each methodology and contrast the improvement of each (within factors).For training group. Both methodologies have a similar distribution of activities to accomplish withing the training. Each group will be evaluated to determine if some activity yielded to a more significant difference in the overall performance (between factors).Finally, and mainly, for AT methodology groups to analyze and compare the final performance between the game-based experimental groups and the non-game-based control group and conclude if there is a significant difference between them.

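### The sample size of 34 is computed correctly, but the effect size called moderate is, for this interaction, a 1.0 SD difference in improvement between two active trainings, and it rests on an unstated pre-post correlation of 0.5

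*Protocol article*

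**What the plan says.** All the inputs stand in the protocol article under *Sample size, inclusion & exclusion criteria*.

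- Test: "Sample size was calculated determining F-tests family for ANOVA repeated measures between and within interactions".
- Inputs: "given a moderate effect size of 0.25, alpha error prob of 0.05 and power of 0.80, two groups and two measurements".
- Result: "G*Power 3.1 points a total sample size for both groups of 34". Forty are to be recruited, 20 per group, allowing for about 10% loss.
- Basis of the effect size: earlier work in which "effect sizes of behavioral auditory discrimination measurements are reported from moderate to large", with Cohen's d and Cohen's f cited together.

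No pre-post correlation is given, and 0.25 is not translated into a difference in improvement between the two trainings.

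Under *Expected outcomes & analysis*, "The primary outcome measures are related to neuro audiological changes in auditory processing", with mismatch negativity (MMN) and P3 named. The same section makes the comparison of the two training methods the main one. Under *AT experimental design*, both arms train on identical modules for an equivalent 15 hours.

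**The concern.** A reader who sees a moderate effect and 80% power will picture a difference of about half a standard deviation between arms. That reading suits f = 0.25 in a simple comparison of two group means, where d = 2f = 0.5. It does not suit the test that was powered. In a 2×2 within-between interaction the same f stands for a difference in pre-post change twice that size.

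The contrast isolates what game elements add to otherwise equivalent active training, so the size of the assumed difference matters for interpretation. If the main comparison is not significant, the sample size statement as worded invites the conclusion that a moderate advantage has been made unlikely. Under the correlation implied by the protocol's own figure, a 0.5 SD advantage would be missed about 70% of the time.

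A further, smaller point: the cited effect sizes are behavioural, while the named primary measures are evoked potentials.

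**Working it through.** **Inputs from the article.** f = 0.25 (read as Cohen's f, because it is entered in the F-test family); α = 0.05; target power 0.80; k = 2 groups; m = 2 measurements; 34 participants calculated, 40 recruited, about 10% loss (40 × 0.9 = 36 completers).

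**Assumption.** The pre-post correlation ρ is not stated. It is inferred in step 1 and varied in step 4.

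**Step 1: reproduce 34.** For the within-between interaction, λ = f²·N·m/(1 − ρ), with df₁ = (k − 1)(m − 1) = 1 and df₂ = (N − k)(m − 1) = N − 2.

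With ρ = 0.5 and N = 34: λ = 0.0625 × 34 × 2/0.5 = 8.5, on F(1, 32), and power = 0.807. With N = 32: λ = 8.0 and power = 0.781. So 34 is the smallest even total that reaches 0.80.

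Other correlations give other totals: 66 at ρ = 0, 46 at 0.3, 40 at 0.4, 28 at 0.6 and 22 at 0.7. Of the values tried, only ρ = 0.5 returns the protocol's figure.

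**Step 2: translate f = 0.25.** Let D be the difference between arms in mean pre-post change. The four interaction effects are ±D/4, so f = D/(4·SD) and D = 4 × 0.25 × SD = 1.0 SD, in raw-score units. Check: cell means of 0, 0, 0 and 1 SD leave interaction residuals of ±0.25 SD, which is f = 0.25. This holds for any ρ.

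The SD of change is SD·√(2(1 − ρ)). At ρ = 0.5 it equals the raw SD, so D is also d = 1.0 on change scores. Cross-check: a two-sample t test on change with 17 per arm and d = 1.0 has power 0.807, the same as in step 1.

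**Step 3: power for 0.5 SD of change.** This is a two-sample t test on change scores with d = 0.5. At ρ = 0.5 it corresponds to f = 0.125.

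| Completers | Power, d = 1.0 on change | Power, d = 0.5 on change |
|---|---|---|
| 34 | 0.807 | 0.293 |
| 36 | 0.830 | 0.308 |
| 40 | 0.869 | 0.338 |

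Eighty per cent power for d = 0.5 on change would need 128 completers in total (64 per arm).

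**Step 4: dependence on the correlation, N = 34.** Both differences are now held fixed in raw-score SD.

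| ρ | Power, 1.0 raw SD (f = 0.25) | Power, 0.5 raw SD (f = 0.125) |
|---|---|---|
| 0.3 | 67% | 22% |
| 0.5 | 81% | 29% |
| 0.6 | 89% | 35% |
| 0.7 | 95% | 45% |
| 0.8 | 99% | 61% |
| 0.9 | >99% | 89% |

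If the 0.5 SD is in change-score units, the step 3 figures apply whatever ρ is.

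**Step 5: what the planned size can detect.** Solving the t-test power for d on change: with 36 completers, 80% power is reached at 0.96 SD and 50% at 0.67 SD; with 40, at 0.91 SD and 0.64 SD.

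**The case against.** The strongest reply is that nothing has been miscalculated. The stated inputs return 34, the interaction test suits the planned ANOVA, and the claim of 80% power at 0.25 is true as written. A reader might infer a sample size error, or that the real power is 30% and not 80%. Neither follows: 81% and 29% are powers for two different effects, and the article never claims 80% for 0.5 SD. That benchmark is the common convention for a moderate d, not a figure from the protocol. Moreover, 0.25 is the conventional medium value of Cohen's f. All of this stands. What remains is that the conventional label, carried into this interaction and justified by d and f together, describes a 1.0 SD difference in change.

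The reply that a higher correlation would restore power is partly right. In raw-score units at 34 completers, power for 0.5 SD reaches 61% at ρ = 0.8 and 89% at 0.9. The article offers no such correlation, and its own total implies 0.5.

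A reader might also infer that the trial can see only very large differences. Step 5 shows that this goes too far: with 40 completers it has even odds of detecting 0.64 SD of change.

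On the behavioural source, the primary-outcome paragraph also registers a count of discrimination trials, and the aim includes behavioural performance. Behavioural evidence is therefore relevant, though it does not cover MMN and P3. Whether the cited studies report interaction effects or used active comparators cannot be checked from the article.

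Finally, the article nowhere says that non-significance will be read as equality; that is a risk of interpretation, not a stated plan. An article may also leave the correlation and the reporting of confidence intervals to a fuller document, so their absence alone is not the point.

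**Conclusion.** The point holds as a matter of labelling and disclosure, not arithmetic. The total of 34 is right for f = 0.25 with a pre-post correlation of 0.5. For this 2×2 interaction that f is a 1.0 raw-SD difference in improvement between arms at any correlation, and d = 1.0 on change scores at 0.5. Calling it moderate gives the 80% a meaning that the design does not deliver.

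For 0.5 SD of change, power is 29% to 34% across 34 to 40 completers, so full retention does not alter the picture. In raw-score units this figure depends on the correlation. The conclusion rests on reading 0.25 as Cohen's f, on the inferred correlation, and on the usual convention for a moderate d.

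It should be fixed because it bears on what the main between-method comparison can claim. It does not call the size or conduct of the trial into question.

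**What to change.** Keep recruitment at 40 and replace the effect-size sentence with wording such as:

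> Thirty-four completers give 81% power to detect a 1.0 SD greater pre-post change in one arm than in the other, assuming a pre-post correlation of 0.5. Power for a 0.5 SD difference is about 30% under the same assumption.

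In addition:

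- Remove the adjective *moderate* from the effect size.
- Note that the sources for the effect size are behavioural and do not cover the MMN and P3 primary outcomes.
- State that a non-significant interaction will not be interpreted as equal performance of the two trainings. Reporting the between-arm difference in change with a 95% confidence interval would support this, but is secondary.

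The cost is wording only: no extra participants and no change to the analysis. The downside is that the stated sensitivity becomes less favourable.

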### Study design & setting

This work is divided in three instances: 1) development and validation of the digital game, 2) implementation and evaluation of the ADT game performance in auditory improvement, 3) comparison between both methodologies.

The first stage consists of serious game development. This stage is divided into two sub-stages. First one is back-end development (auditory tasks) and tests and second one is front-end development (interactive elements) and tests, additionally both are having their respective correction sub-stages.

Second stage consists in the implementation of the game-based ADT, as described in Fig 3. In 30-minutes sessions (15 hours total), the 40 participants will be treated by ADT; 20 participants will use the game-based and 20 participants will be treated by a non-game-based training procedure with the same four modules in both cases. Both procedures will locally save training data in participant computer, which will be gathered each week.

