**Fig 3 pone.0313478.g003:**
[figure not shown]
Protocol steps. 1) Game-Based AT is first developed and validated through perceived usability evaluation questionnaires. 2) Assessments are done before and after AT is implemented for two sample groups. 3) Finally AT effectiveness is measured and compared through groups performance and AEPs.

The participant will be introduced to the study, explaining to them the informed consent and the confidentiality criteria. Participants will be given their audiometry results and a beginner game kit, also they will receive an online-shop gift card ($5-$25 us) if they finish the training levels satisfactorily, based on constant and consistent game playing, meaning they accomplish daily training and completely succeed in all training levels. Participants will also receive hearing health information after intervention and the option of scheduling a medical appointment with the otorhinolaryngologist and/or audiologist if they desire.

Auditory assessments will be conducted in noise-controlled rooms within university buildings or hospitals. Eligibility screen, informed consent and pure tone audiometry will be carried before allocation. Procedure to follow will be explained to them, beginning the pure-tone audiometry (air and bone) procedure. The participant will be indicated to raise the hand when they start to listen to the stimuli.

Then, they will be introduced to the electrode placements. Electrodes (Fz, F3, F4, Cz, C3, C4, T7 & T8) will be placed, and conductive gel will be applied to reduce the electrode-skin impedance. Calibrated headphones will be placed carefully. The participant will be asked to remain seated and still during evaluation. This process will be applied for the pre and post training assessment.

As shown in Fig 4. basal state will be recorded for 60 s in opened and closed eyes conditions. Then oddball paradigm will be used to assess auditory discrimination in pitch, intensity, duration and localization of the stimuli. P300 & Mismatch Negativity Potentials will be assessed by this paradigm in attentional and non-attentional conditions.

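### Simple 1:1 randomisation does not guarantee the 20 per group that the protocol states as fixed; the method or the numbers need rewording

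*Protocol article*

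**What the plan says.** All the relevant statements are in the protocol article.

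- Method (Sample size, inclusion & exclusion criteria): assignments "will be randomized using simple randomization 1:1 allocation ratio".
- Total (same section): "A total of 40 participants will be recruited and enrolled in the study".
- Group sizes (same section): "Sample size for each group (non-game-based ADT and game-based ADT) is 20 individuals each". Just before this, after the calculated total of 34, it says that the "sample size for Group A (control), and Group B (experimental) will be equally distributed".
- Group sizes again (Study design & setting): "20 participants will use the game-based and 20 participants will be treated by a non-game-based training procedure".

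Exactly 20 per group is therefore stated twice, and equality without a number once. The text mentions no blocks, restricted list or replacement rule that would produce equal groups. The paragraph after the Fig 1 caption adds that neither participants nor the staff who analyse the data are blinded.

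**The concern.** Simple randomisation is in effect a separate fair coin toss for each participant. A 1:1 ratio under that method describes the chance on each toss, not the final count. The protocol nevertheless presents 20 and 20 as what will happen. This is not a detail left to a fuller document: the article names a method and states a result that the method does not ensure.

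Two things are at stake. The first is group size, because uneven groups carry somewhat less information than even ones of the same total. The second matters more. Staff who are told both to randomise simply and to finish with 20 per group may accept unequal groups and depart from the stated sizes, or may close a group once it reaches 20. In the second case every later assignment is certain, and in an open-label trial anyone who keeps count can see it coming. That would allow knowledge of the next assignment to affect who is enrolled and when.

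**Working it through.** **Inputs.** From Sample size, inclusion & exclusion criteria: 40 participants; simple randomisation at 1:1, so probability 0.5 each; f = 0.25; alpha = 0.05; target power 0.80; two groups; two measurements; calculated total 34; expected loss about 10%. The pre-post correlation rho is not given. I take 0.5 and vary it below.

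**Step 1: reproduce the plan's own figure.** For the within-between interaction, the noncentrality is lambda = f² × N × m / (1 − rho), with m = 2 measurements and 1 and N − 2 degrees of freedom.

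- N = 34, rho = 0.5: lambda = 0.0625 × 34 × 2 / 0.5 = 8.5, power 0.807.
- N = 32: lambda = 8.0, power 0.781.

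So 34 is the smallest even total that reaches 0.80 at rho = 0.5, as the protocol reports. Allowing for 10% loss, 34 / 0.90 = 37.8, rounded up to 38, which 40 covers.

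**Step 2: distribution of group sizes.** Under simple randomisation the size of one group is Binomial(40, 0.5).

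- P(20/20) = C(40,20) / 2⁴⁰ = 137,846,528,820 / 1,099,511,627,776 = 0.1254.
- P(22/18 or more uneven) = 1 − P(19 to 21) = 1 − 0.3642 = 0.636.
- P(24/16 or more uneven) = 1 − P(17 to 23) = 1 − 0.7318 = 0.268.
- The expected absolute difference between groups is 5.0 participants.

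**Step 3: cost in power.** For sizes n1 and n2, lambda is multiplied by 4 × n1 × n2 / N². With all 40 analysed and rho = 0.5:

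| Split | Multiplier | lambda | Power |
|---|---|---|---|
| 20/20 | 1.00 | 10.0 | 0.869 |
| 24/16 | 0.96 | 9.6 | 0.855 |
| 28/12 | 0.84 | 8.4 | 0.806 |
| 29/11 | 0.7975 | 7.975 | 0.786 |

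Power stays above 0.80 down to 28/12; a more uneven split has probability 0.006. With 10% loss (36 analysed, the same proportions in each group), power is 0.830 for an even split, 0.815 starting from 24/16 and 0.794 starting from 26/14. A split of 26/14 or more uneven has probability 0.081.

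**Step 4: sensitivity to the assumed correlation.** Power at 20/20 and at 24/16, with 40 analysed:

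| rho | 20/20 | 24/16 | Loss |
|---|---|---|---|
| 0 | 0.587 | 0.570 | 0.017 |
| 0.3 | 0.740 | 0.723 | 0.017 |
| 0.5 | 0.869 | 0.855 | 0.014 |
| 0.7 | 0.978 | 0.974 | 0.004 |

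The absolute power depends heavily on rho, but the loss from a 24/16 split is below 0.02 throughout.

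**The case against.** The strongest reply is that this is loose terminology. The investigators may have a pre-generated random order of 20 + 20 places and simply call it simple 1:1 randomisation. That would give equal groups without anyone closing a group by hand. The document does not rule this out, so closing a full group is one possible route and not an established practice. The inconsistency stands even so, because such a list is a restricted scheme and the article does not say so.

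A second reply is that the effect on power is slight. That is correct, and the point does not rest on power.

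A third is that any scheme with a fixed total lets someone who tracks earlier assignments deduce some of the last ones, while unrestricted simple randomisation is the least predictable method. This also stands. It is why concealment of the list belongs in the fix, and why keeping simple randomisation is an acceptable alternative.

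A reader might infer more than the text supports, in three ways:

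- *That 20/20 is unattainable.* It is the single most likely split; it is only not guaranteed.
- *That a group of 16 breaches a requirement of 17.* The protocol gives a total of 34, and 17 is merely half of it. At rho = 0.5, a 24/16 split of 40 has more power (0.855) than 17/17 (0.807).
- *That the baseline EEG and the discrimination questionnaire are taken after the group is known.* Study design & setting says "Eligibility screen, informed consent and pure tone audiometry will be carried before allocation", but it does not place the other baseline measurements after allocation. The schedule in Fig 1 is not shown, and the text following it puts the training demonstration after consent and tests. The timing therefore cannot be called a defect.

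**Conclusion.** The inconsistency is real: the named method does not have the property that the protocol states twice as a number and once as equal distribution. Under simple randomisation, about seven trials in eight would miss 20/20 (1 − 0.125 = 0.875), and about one in four would be at 24/16 or worse. These probabilities need only independent assignment with probability 0.5 and 40 participants.

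The statistical cost is minor, a loss of less than 0.02 in power at 24/16 for any correlation from 0 to 0.7. The absolute figures of 0.869 and 0.855 hold only for the assumed correlation of 0.5. The reason to correct the text is the risk to unpredictable allocation if staff try to meet both statements in an open-label trial. It should be corrected, but it does not threaten the trial's validity as designed.

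**What to change.** Choose one of two wordings.

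1. **Fixed sizes.** Replace the reference to simple randomisation with a computer-generated restricted list of 20 per group, for example permuted blocks of varying, undisclosed size. State that the list is concealed from those who enrol participants. This gives 20/20 with certainty if all 40 are enrolled.
2. **Random sizes.** Keep simple randomisation, and describe 20 per group as the expected size wherever the article now states 20 or equal distribution. At rho = 0.5, average power over the possible splits is about 0.860 with 40 analysed, against 0.869 for an exact 20/20.

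The second costs only wording. The first also needs a new list and someone outside enrolment to hold it. Its small drawback is that the final assignments can be partly deduced by anyone tracking earlier ones, so the list must stay concealed. The article plans enrolment from January 2025, so the change belongs before that. If enrolment has begun, the text should describe the method actually used.

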**Fig 1 pone.0313478.g001:**
[figure not shown]
SPIRIT schedule or enrollment, interventions and assessments for Clinical Trials.

No blinding will be involved within participants nor personnel who analyze data, since they must know which group they belong to, so instructions can be explained and clearly understood.

Participants will be recruited from the Tecnologico de Monterrey student population by local advertising. They will be invited to fill-in a survey to determine and filter, considering eligibility criteria, the participants that are able to be part of the research sample. These selected people will participate in the ADT sessions for a total of 15 hours, informing them about the activities to be done and the main objective. They will be given the informed consent to be read and signed before audiologic tests. After consent and tests are fulfilled, they will be receiving a demo of the training methodology they were assigned to and a tutorial.

Inclusion criteria are the following: Both genre, age between 18 and 30 years old. Volunteers with normal hearing pure-tone thresholds 25 dB HL across frequencies 125–8000 Hz previously evaluated by air-conduction and bone-conduction audiometry.

Exclusion criteria are the following: Participants that do not sign the informed consent, that present hearing loss or impairment pure-tone 25 dB HL, that cannot fulfill the required time for the AT, that is pregnant or that is frequently consuming medicines that can alter the participant state, that is currently enrolled in another auditory training or ear training intervention.

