**Fig 2 pone.0313478.g002:**
[figure not shown]
AT materials. Study materials are shown as to be used in each stage of research. First stage is the development of the training tools in Unity. Second stage is the application of auditory assessment for auditory processing screening which will be managed in two sessions of 50 minutes. Third stage refers to the application of auditory training during 15 hours. Fourth stage refers to the data management.

ADT Game will be developed to enhance user experience and favor attention through task engagement. ADT Game will consist in basic sound features discrimination training (pitch, intensity, duration and localization). Each participant will use personal computer and calibrated headphones to receive training. For auditory game-based and non-game-based training, Unity Software and IDE Visual Studio Code (C#) will be used to generate stand-alone applications for both Windows and Mac OS.

For neuro-audiological assessments audiometer Interacoustics AD226 with audiometric headset DD45 and B71 Bone conductor will be used to conduct pure-tone tests and Unicorn Hybrid Black 8-channel EEG (250 Hz), with electrode placement using the 10–20 system, and calibrated headphones Senheisser SRH440 (10–22,000 Hz) will be used to manage AEPs.

A brief basic auditory discrimination performance questionnaire (ADPQ) was designed for addressing participant’s discrimination and complementary conditions during and after each of experimental acoustic features under attentive processes. Questionnaire (I-CVI > 0.875) consists of 7 items evaluating in a 4-point likert scale the performance status of the participant (perceived state and perceived performance). This questionnaire helps the present study to have a perceptual participant’s discrimination response and to reduce participant’s state bias during the assessment.

For acquisition software, OpenVibe will be used to record EEG signals and Built-in App developed in Super Collider will be used for sound reproduction using a self-designed application to make easier the adjustment of multiple acoustic feature paradigms.

For data software, EEGLAB Matlab toolbox will be used for processing and analysis of EEG recorded data. Matlab software will be used for data analysis obtained from participants performance during training and as result of the auditory assessments.

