**Fig 4 pone.0313478.g004:**
[figure not shown]
Auditory discrimination paradigm procedure. Basal state is only recorded at the beginning of the session. In each of the feature variation the rest of the procedure is repeated.

Sound system used for stimuli is integrated by a sound interface (DAC/ADC) with supra-aural Shure SRH 440’ headphones system calibrated to audiometric reference of 1kHz to 70 dB HL. Sound stimuli consists in pure tones lasted with 100 ms duration and with a 900 ms ISI as the standard stimuli. Deviant stimuli vary in each of the four testing sound features (pitch, intensity, duration and localization). EEG event related activity will be processed in Matlab with EEGLab, for preprocessing and epoching (−200ms, 600ms)”.

For the AT, digital tools will be shown to participants, they will be instructed in how to use it, and main features will be explained. They will be told to use it daily for 30 minutes indicating the modules to evaluate in each week sessions. Game data (training time, response time and correct responses) will be gathered for participants after each week to register in-game indicators. They will be asked not to do more or less time than indicated, if indication is not followed, they will not be eligible to continue participating. An extra explanatory video will be provided with a user manual.

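### The protocol leaves the people who analyse the EEG unblinded for a reason that fits only participants and instructors; the MMN and P3 measures could be derived from coded files at little cost

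*Protocol article*

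**What the plan says.** The blinding statement follows Fig 1 in the protocol article's section on sample size, inclusion and exclusion criteria: "No blinding will be involved within participants nor personnel who analyze data, since they must know which group they belong to". The sentence goes on to give the purpose: "so instructions can be explained and clearly understood".

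The Expected outcomes & analysis section says "The primary outcome measures are related to neuro audiological changes in auditory processing" and specifies that "AEPs to be obtained are Mismatch Negativity and P3 components (continuous"). A count of discrimination trials is listed beside them. For the evoked potentials, the same section says "it is expected an increase in evoked potentials amplitude and a decrease in latencies".

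On processing, the Materials section says "EEGLAB Matlab toolbox will be used for processing and analysis of EEG recorded data". Study design & setting says "EEG event related activity will be processed in Matlab with EEGLab, for preprocessing and epoching", with an epoch of −200 to 600 ms.

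The article describes no coding of EEG files, no blinded rater and no automated pipeline with settings fixed in advance.

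**The concern.** The decision and its reason do not match. Participants must know which tool they use, and so must whoever gives the demo and tutorial. Someone cleaning a recording or measuring a component needs neither the arm nor the visit.

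Participants cannot realistically be blinded, because the plain interface and the game differ visibly (Group A and Group B sections). Masked derivation of the outcome is then the main safeguard left against expectation effects, and the protocol gives it up without a reason that applies. Randomisation does not protect against bias that enters when a recording is processed after allocation.

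At stake is the between-group comparison of MMN and P3. If judgement enters and is influenced by knowledge of the arm, a difference could appear with no true effect behind it, or a true difference could be distorted. The project develops the game it evaluates, and the Abstract already presents game-based approaches as adding to traditional training. An expectation in favour of the game arm is therefore plausible.

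**Working it through.** **1. Does the stated reason reach the people it names?**

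| Who | Needs the arm to give or follow instructions? | Named as unblinded? |
|---|---|---|
| Participants | Yes | Yes |
| Staff giving the demo and tutorial | Yes | Not named separately |
| Personnel analysing data | No | Yes |

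The reason fails for the third row. If the same people instruct and analyse, they will know the allocation list, but the files they process can still be coded.

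**2. Does analysing data include processing the EEG?** The article does not name EEG processors separately. The Materials section assigns both processing and analysis of the EEG to EEGLAB, so reading the sentence to include them is reasonable. It remains an inference.

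**3. Which outcomes are exposed?** MMN and P3 amplitude and latency are derived from a processed waveform, so they can be. The number of discrimination trials is a count and needs no waveform reading.

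**4. The plan's own sample size, for background.** The inputs are "given a moderate effect size of 0.25, alpha error prob of 0.05 and power of 0.80, two groups and two measurements". For the within–between interaction, λ = f² × N × m / (1 − ρ), with 1 and N − 2 degrees of freedom. The correlation ρ is not stated; 0.5 is assumed here. With N = 34, λ = 0.0625 × 34 × 2 / 0.5 = 8.5 on 1 and 32 df, and power is 0.807. The stated total of 34 reproduces. The 40 recruited, less about 10%, leave 40 × 0.9 = 36, or 18 per arm. The blinding point does not depend on these figures; they only set the group sizes for step 5.

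**5. Illustration of what a bias would do.** The documents give no size of bias, so a range is assumed. With two groups and two visits, the group-by-time test is equivalent to a two-sample t-test on change scores. Suppose there is no true effect and one arm's change scores are shifted by b SD. The noncentrality is b / (2/√N) = b√N / 2, with N − 2 degrees of freedom, tested two-sided at 0.05.

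| Assumed shift b | Noncentrality, N = 36 | Error rate, N = 36 | Noncentrality, N = 40 | Error rate, N = 40 |
|---|---|---|---|---|
| 0 | 0 | 5.0% | 0 | 5.0% |
| 0.1 | 0.30 | 6.0% | 0.32 | 6.1% |
| 0.2 | 0.60 | 9.0% | 0.63 | 9.5% |
| 0.3 | 0.90 | 14.1% | 0.95 | 15.2% |

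These are error rates conditional on an assumed shift. They do not estimate what will happen in this trial.

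**The case against.** The strongest objection is that the judgement steps are inferred. A reader might conclude that epochs will be rejected by hand and peaks picked by eye. The article names only preprocessing, epoching and analysis in EEGLAB. Rejection criteria and measurement windows are details that a condensed article commonly leaves to the full protocol or analysis plan, and their absence here is no fault. If the pipeline is scripted and fixed in advance, most of the route for bias closes. This stands, so the concern is conditional on judgement being used. It does not remove the point: declining to blind the analysts is a stated choice with a stated reason, and a fuller plan that blinded them would contradict it.

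A reader might also take the stated direction, larger amplitudes and shorter latencies, as evidence of an expectation favouring the game arm. It is not. The section describes change from before to after training and does not say that one arm should change more. A bias tied only to visit would push both arms the same way and largely cancel in the group comparison. Support for an arm-specific expectation comes from the Abstract and from the project's development of the game.

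It is equally tempting to say that nobody needs the labels even to fit the model. The ANOVA needs visit and at least a masked group label, so the point concerns EEG processing and measurement.

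Finally, masking may not be free or complete. Staffing is not described, and people who ran the sessions may recognise recordings. This stands as a limit on what the fix achieves.

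**Conclusion.** The point holds in limited form. The protocol leaves its analysts unblinded for a reason that does not apply to them, and nothing in the article offsets this for the evoked-potential part of the primary outcome. That mismatch is plain in the text.

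Whether bias will occur, and how large it would be, cannot be determined from the documents. The error rates of about 6%, 9% and 14–15% rest on assumed one-arm shifts of 0.1, 0.2 and 0.3 SD, no true effect, and 18 to 20 participants per arm. A reader might infer that the primary outcome as a whole is compromised. The documents do not support that: the discrimination-trial count is not exposed to this mechanism, and manual EEG handling is not stated. The change is worth making because it removes an avoidable risk at small cost.

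**What to change.** Restrict the blinding statement to participants and the staff who instruct them, and add wording such as:

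*EEG files will be stored under random codes that show neither arm nor visit. Preprocessing, epoch rejection and measurement of MMN and P3 amplitude and latency will be carried out on the coded files. The evoked-potential dataset will then be locked, after which visit and group will be linked for the ANOVA.*

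Group can stay masked under two neutral labels until the model has been run. The labels should not be A and B, because the protocol already uses these for control and experimental.

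The cost is a renaming script, a code key held by someone who does not process the files, and a short delay before linkage. No participants, visits or equipment are added. Masking may be imperfect if the same people recorded the sessions; the report should say so if that is the case. The change concerns only recorded files, so it can be adopted at any time before EEG processing begins.
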